#### Secondary analyses

As a sensitivity analysis to the primary efficacy analysis, the same test will be repeated on the per-protocol population including all patients without major protocol violations. As another sensitivity analysis, the primary hypothesis will also be evaluated by computing the restricted mean survival at 5 years. Event probabilities of DFS will be estimated by Kaplan-Meier-Curves. The above analyses will be repeated for overall survival. The influence of treatments received after the period of intervention on DFS and OS will be assessed. Specific post-study treatments will be included in the piecewise exponential model as time-dependent explanatory variables. Longitudinal models will be fitted to examine the evolution over time of the two arms and to test potential differences between them. Circulating tumor DNA, tumor markers and molecular information as well as quality of life/ patient reported outcomes will be evaluated exploratory.

The intent-to-treat population includes all randomized patients. Treatment assignment is based on the randomized treatment (primary population). The ITT population is the primary population for the description of the patient and treatment characteristics and is used for the primary efficacy analysis. The per-protocol (PP) population will include all randomized patients fulfilling the inclusion and exclusion criteria and who received at least one cycle of active treatment with at least one documented structured follow-up visits (arm A) or with at least one documented follow-up visit (arm B). Treatment assignment is based on the treatment actually received. Patients with major protocol violations will be excluded.

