## Abstract

**Background:**

Standard of care for non-metastatic colon cancer is surgery followed by stage-guided adjuvant therapy and/or structured follow-up. Upfront surgery in resectable colon cancer is irrespective of local T/N stage, whereas adjuvant systemic therapy is recommended according to pathological staging. The role of neoadjuvant chemotherapy remains unclear. Whereas perioperative systemic therapy in colon cancer seems to be safe and may lead to pathologic downstaging, evidence on improved survival and quality of life remains scarce. The PROTECTOR / FIRE‑10 trial aims to generate evidence that perioperative systemic therapy improves survival without compromising quality of life in locally advanced, mismatch-repair proficient colon cancer patients.

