## Methods/design

### Aim of the study

The main objective of this randomized multicenter trial is to generate further evidence that preoperative chemotherapy improves disease-free survival in patients with advanced colon or upper rectal cancer.

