### Sample size

Based on the best available evidence described above [9, 10], 2-year DFS rate is 70% in the straight to surgery group and we hypothesize that DFS rate will be 78% in the neoadjuvant treatment followed by surgery group. To demonstrate an increase of 8% points in 2-year DFS rate (hazard ratio = 0.696), it is required to observe 271 DFS events, with the recruitment of 714 (476:238 per arm) patients with an allocation ratio of 2:1 (experimental vs. standard). These calculations assume that the DFS time follows a piecewise exponential distribution with two strata within the maximum follow up time ([0–2] years [2–8], years). For the first stratum, we assume that DFS rate will be 70% after 2 years in the control group. For the second stratum, we expect a level-off effect to a plateau of 60% DFS rate after 8 years. The sample size was calculated with 2-sided 5% level of significance, 80% power, with 5-year recruitment and 5-year follow-up periods and 5% drop-out in the first two years. The event rate in the straight to surgery group will be monitored annually by the independent data monitoring and ethics committee to ensure the baseline assumptions are appropriate. An interim analysis for efficacy will not be conducted. Given that an inferiority is unlikely with the background of TNT concepts in rectal cancer and previous trials and the increased sample size would impact on the feasibility of recruitment, interim analyses will solely focus on safety.

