### Quality of life

Quality of life (QoL) as assessed with the QoL questionnaire EQ-5D-5L

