### Statistical analyses

#### Primary analysis

The null hypothesis to be tested in confirmatory analysis states that the hazard ratio for DFS comparing intervention versus control equals 1. This hypothesis will be tested by means of piecewise exponential model, by dividing the maximum follow-up time in 2 strata (0–2 years, 2–8 years), assuming the hazard is approximately equal in each time interval. This regression will be adjusted for the strata for randomization mentioned above. The two-sided significance level is set to 0.05. The primary analysis will be conducted based on the full analysis set which is defined as the intention to treat population. In a survival analysis setting, missing values are treated as non-informative censoring values so there is no need for imputation. 

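### The abstract aims to show that quality of life is not harmed, but the plan only evaluates it as exploratory and tests for differences, which cannot support a no-harm statement

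*Protocol article*

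**What the plan says.** The Background paragraph of the abstract describes the trial as aiming to generate evidence that "perioperative systemic therapy improves survival without compromising quality of life". The abstract's Methods and design paragraph then lists patient-reported quality of life beside efficacy and safety among the things investigated.

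In the body, the endpoint is "Quality of life (QoL) as assessed with the QoL questionnaire EQ-5D-5L". It has its own heading, ahead of and apart from the exploratory endpoints.

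Secondary analyses contains two relevant sentences, one directly after the other. The first is: "Longitudinal models will be fitted to examine the evolution over time of the two arms and to test potential differences between them". It does not name the outcome to be modelled. The second says, among other items, that "quality of life/ patient reported outcomes will be evaluated exploratory".

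Two other places limit what the trial sets out to confirm. Aim of the study gives the main objective as to "generate further evidence that preoperative chemotherapy improves disease-free survival", with no mention of quality of life. Primary analysis gives one confirmatory null hypothesis, that "the hazard ratio for DFS comparing intervention versus control equals 1".

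**The concern.** To say that a treatment does not harm quality of life, the data must exclude a loss large enough to matter. In practice the confidence interval for the arm difference has to lie above a stated loss. A difference test answers another question: whether zero can be rejected. Failing to reject zero is compatible with no loss, and also with a real loss that the data were too imprecise to show. An exploratory evaluation with no decision rule establishes neither.

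The direction of the error matters. If a non-significant result were taken as support for the abstract's aim, incomplete questionnaires would help the claim, because less data make non-significance more likely.

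Quality of life is also a main cost to set against any DFS gain. Arm A is assigned about 12 weeks of preoperative chemotherapy. The Discussion accepts that some over-staged patients in that arm will receive chemotherapy for which their true stage would not have qualified them after upfront surgery.

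**Working it through.** **Text against text.** The abstract makes a no-harm claim. The analysis text offers a difference test (outcome not named) and an exploratory label. No sentence in the article links a quality-of-life result to a no-harm conclusion.

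**The plan's own figures.** None is given for quality of life. Sample size has figures for DFS only, at "2-sided 5% level of significance, 80% power". The 271 events reproduce with Schoenfeld's formula, 2:1 allocation and HR = ln(0.78)/ln(0.70) = 0.6966:

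(1.96 + 0.84)² / [(2/3)(1/3)(ln 0.6966)²] ≈ 271.

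This says nothing about precision for EQ-5D-5L.

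**Inputs for quality of life**
- Patients: 476 in arm A and 238 in arm B (Sample size).
- SD of the EQ-5D-5L index: assumed 0.20, range 0.15 to 0.25.
- Share c of patients with usable data: assumed 80%, range 60% to 100%, equal in both arms and missing at random.
- One contrast per patient, normal approximation. A repeated-measures model could do somewhat better.

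**Formulas**
- SE = SD × √[1/(476c) + 1/(238c)]
- Chance that a true loss δ is non-significant (two-sided 5%) = 1 − Φ(δ/SE − 1.96)
- Power to show no harm at margin m when there is no true difference = Φ(m/SE − 1.96)

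**Base case.** SE = 0.20 × √(1/380.8 + 1/190.4) = 0.20 × 0.0888 = 0.0178.
- Loss of 0.04 (0.20 SD): 0.04/SE = 2.25, and 1 − Φ(0.29) = 38% missed.
- Loss of 0.06 (0.30 SD): 0.06/SE = 3.38, and 1 − Φ(1.42) = 8% missed.

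**Range: chance of missing a loss**

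| SD | True loss | 100% complete | 80% | 60% |
|---|---|---|---|---|
| 0.15 | 0.04 | 8% | 15% | 26% |
| 0.20 | 0.04 | 29% | 38% | 50% |
| 0.25 | 0.04 | 48% | 56% | 66% |
| 0.15 | 0.06 | 0.1% | 0.5% | 3% |
| 0.20 | 0.06 | 3% | 8% | 17% |
| 0.25 | 0.06 | 14% | 23% | 35% |

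In every row, lower completion raises the chance that a real loss is missed.

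**Is an interval-based rule feasible?** The smallest margin with 80% power, if there is no true difference, is (1.96 + 0.84) × SE. That is 0.22 SD at full completion, 0.25 SD at 80% and 0.29 SD at 60%. At SD 0.20 these are 0.044, 0.050 and 0.057. In the base case, power is 92% at a margin of 0.06 and about 62% at 0.04.

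**Like with like.** By these formulas, the chance of missing a loss x is one minus the no-harm power at margin x. Setting 38% missed (at 0.04) against 92% power (at 0.06) would therefore compare two thresholds, not two methods. The interval rule does not add precision. Its merit is that imprecise data make the claim harder to reach. It is also not error-free: with a margin of 0.06 and a true loss of 0.04, no harm would still be declared with probability Φ(0.02/0.0178 − 1.96) ≈ 20%. The choice of margin therefore matters.

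**The case against.** The strongest reply is that the plan promises no quality-of-life conclusion. The no-harm phrase stands only in the abstract's background. The section on the aim names DFS alone, the confirmatory hypothesis is DFS alone, and the exploratory label is the cautious choice. The model sentence does not mention quality of life. A margin, time window and interval rule could sit in the full protocol or the statistical analysis plan, neither of which is shown.

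Much of this stands. A reader might infer that the plan will treat a non-significant result as proof of no loss. The article contains no such rule, so this is a possible misreading and not a planned one. A reader might also infer that the longitudinal-model sentence is the stated quality-of-life test. That is likely, since DFS and overall survival are handled by time-to-event methods, but it is not said. If it is wrong, only the exploratory label remains, and that supports the no-harm phrase even less. Nor is the absence of a margin a finding in itself.

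It is also fair that large losses would mostly be seen. A loss of 0.25 SD would be missed 12% of the time with full data and 20% at 80% completion.

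What the reply does not remove is the mismatch. The abstract states as an aim something that the described analyses cannot deliver, and an analysis plan that follows the article's wording would inherit the conflict.

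**Conclusion.** The point holds as a mismatch between the abstract's aim and the analysis described for quality of life. A difference test or an exploratory evaluation cannot support a statement that quality of life is not harmed, and a non-significant result could be mistaken for one.

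The risk is material for small losses and modest for larger ones: in the base case about 38% for a loss of 0.04 (8% to 66% over the range) and about 8% for 0.06. These figures rest on assumed SDs, completion rates and losses, because the article gives none.

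The documents do not support calling this a failed co-primary aim. Quality of life has no confirmatory status, and the DFS conclusion is not touched. What is affected is what the trial may later say about quality of life.

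**What to change.** Choose one of two changes.

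**(a) Keep the no-harm phrase and give it a rule.** Quality of life can stay non-confirmatory. Report the intention-to-treat arm difference in EQ-5D-5L, over a period anchored at randomisation so that arm A's preoperative chemotherapy and arm B's surgery and any adjuvant phase both count, with a 95% confidence interval. Say that quality of life is not compromised only if the lower limit lies above a margin that the sponsor fixes before comparative quality-of-life data are seen. The trial is open-label and already recruiting, so this should be done soon. The length of the period is the sponsor's choice. Name the outcome in the longitudinal-model sentence.

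**(b) Remove the no-harm phrase from the aim**, in line with Aim of the study and Primary analysis, and state that a non-significant difference in quality of life will not be read as absence of harm.

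Both are wording changes to the protocol and analysis plan, with no extra patients or data collection. Under (a) the sponsor must commit to a margin and may have to report that no harm was not shown. Under (b) the sponsor gives up the claim.

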### Primary endpoint

Disease-free survival (DFS) – defined as no surgery, no resection, incomplete resection, disease recurrence (new metastases or local relapse) and death from any cause from the time of randomization. In case of no surgery, no resection, or incomplete resection (defined as R2 resection = macroscopic tumor rest), the timepoint of the respective event will be set to two weeks after randomization to avoid time-bias in favor of the experimental/neoadjuvant therapy arm.

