### Structured follow-up

There will be a structured follow-up for at least 60 months after randomization/treatment, for which several assessments will be necessary. After the structured follow-up, patients will be monitored for DFS and OS in the survival follow-up. The suggested follow-up regimen is shown in Table 2. A deviation by one month is accepted. In case of CT/MRI assessments at any time-point, the sonography of the abdomen might be cancelled at the discretion of the investigator.

**Table 2 Tab2:** Structured follow-up regimen

Investigation	Months in the follow-up (after surgery)							
	3	6	12	18	24	36	48	60
Patient history, anamnesis	x	x	x	x	x	x	x	x
Clinical examination	x	x	x	x	x	x	x	x
CEA assessment	x	x	x	x	x	x	x	x
CT (thorax/abdomen/pelvis)					x			
Abdominal ultrasound		x	x	x	x	x	x	x
Colonoscopy			x					

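### The per-protocol visit rule differs by arm and, on the Table 2 schedule, removes never-operated arm A patients who are DFS events, tilting this sensitivity analysis toward arm A

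*Protocol article*

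**What the plan says.** - **PP membership (Secondary analyses).** Patients must meet the eligibility criteria and be among those "who received at least one cycle of active treatment". By sentence structure this treatment condition belongs to arm A. The visit condition then reads: "at least one documented structured follow-up visits (arm A) or with at least one documented follow-up visit (arm B"). Major protocol violators are excluded, and "Treatment assignment is based on the treatment actually received".
- **Use of the set (Secondary analyses).** The primary DFS test is repeated on it as the first-named sensitivity analysis. The analyses are then repeated for overall survival.
- **Visit schedule (Structured follow-up).** The text says: "There will be a structured follow-up for at least 60 months after randomization/treatment". The column header of Table 2 in the same section reads "Months in the follow-up (after surgery"), and its first visit is at month 3.
- **Endpoint (Primary endpoint).** DFS is "defined as no surgery, no resection, incomplete resection, disease recurrence (new metastases or local relapse) and death from any cause". For "no surgery, no resection, or incomplete resection (defined as R2 resection = macroscopic tumor rest") the event is dated two weeks after randomization, with the stated aim of avoiding a time bias that would favour the neoadjuvant arm.
- **Primary analysis.** The confirmatory test uses the intention-to-treat population.

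**The concern.** Whether a patient has a visit is known only after randomization and depends on outcome. If structured visits start after surgery, an arm A patient who never reaches the operating theatre cannot have one. That patient is a DFS event at week 2 in the primary analysis and absent from the PP analysis. An arm B patient with the same failure can stay in through any follow-up visit. Membership is then selected on the endpoint itself, and differently by arm.

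This works against the week-2 dating rule, which exists to stop bias toward arm A. Failure to reach resection is also a main risk of putting chemotherapy before surgery. A robustness check that loses those patients from the experimental arm cannot test that risk, and an agreeing PP result would be weaker support than it appears. Grouping by treatment received adds a second departure from the randomized comparison.

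**Working it through.** **1. Who is removed, under each anchor**

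| Arm A patient | DFS event? | Table 2 anchor (surgery) | Text anchor (randomization/treatment) |
|---|---|---|---|
| Never operated | Yes, week 2 | Removed | Can stay |
| Dies before first visit | Yes | Removed | Depends on visit date |
| Lost before first visit | Censored | Removed | Depends on visit date |
| Explored, not resected | Yes, week 2 | Can stay | Can stay |
| R2 resection | Yes, week 2 | Can stay | Can stay |

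With the full preoperative course (about 12 weeks) the month-3 visit falls roughly 6 months after randomization, plus an interval to surgery that the article does not state. In arm B it falls about 3 months plus the wait for surgery. A deviation of one month is accepted.

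**2. Inputs (Sample size)**

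Control DFS is 70% at 2 years and 60% at 8 years; allocation is 476:238; recruitment 5 years and follow-up 5 years. The control hazards are −ln(0.70)/2 = 0.178 per year, then −ln(0.60/0.70)/6 = 0.026 per year.

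The plan gives no figure for the PP set. Its event target does reproduce: HR = ln(0.78)/ln(0.70) = 0.6966, and (1.960 + 0.842)² / [(1/3)(2/3)(ln 0.6966)²] = 7.849/0.02905 = 270.2, rounded up to 271.

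The rate *f* of removed-type failures is an assumption, as the article gives none. At 1%, 2%, 3% and 5% it means about 5, 10, 14 and 24 of the 476 arm A patients.

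**3. Upper case: no treatment effect, same *f* in both arms, all dropped in arm A, all kept in arm B**

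If failures come on top of the control hazards, 2-year DFS in the PP set is 0.70 in arm A and 0.70(1 − *f*) in arm B:

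HR = ln(0.70) / ln[0.70(1 − *f*)]

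At *f* = 2%: −0.3567/−0.3769 = 0.946.

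The planned two-piece exponential model was also fitted to simulated trials (failures at week 2; no drop-out, no stratum adjustment). It lies slightly nearer 1, because the years after 2 carry no bias.

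| *f* | Formula HR | Simulated PP HR | False claims for arm A (nominal 2.5%) |
|---|---|---|---|
| 1% | 0.973 | about 0.97 | about 4% |
| 2% | 0.946 | about 0.95 | about 6% |
| 3% | 0.921 | about 0.93 | about 9% |
| 5% | 0.874 | about 0.88 | about 18% |

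The ITT hazard ratio is 1.00 in every row. If the failures are instead counted inside the 70%, the formula ln[0.70/(1 − *f*)]/ln(0.70) gives 0.972, 0.943, 0.915 and 0.856.

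**4. Both arms drop these failures**

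- Equal rates: 0.70 against 0.70, so HR = 1.00 and no bias from this source.
- 5% in arm A, 2% in arm B: ITT 2-year DFS is 0.95 × 0.70 = 0.665 against 0.98 × 0.70 = 0.686, so HR = 0.4080/0.3769 = 1.08. After dropping both groups it is 1.00.
- The same rates with arm B's failures kept: 0.3567/0.3769 = 0.95.

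**The case against.** The strongest defence is that the asymmetry is only in the wording. The article has one visit schedule with no arm-specific version, so arm B's follow-up visit may simply mean a Table 2 visit. Never-operated arm B patients would then drop out too. The text anchor would also let a non-operated arm A patient have a structured visit. Arm B patients without surgery, and crossovers, might be excluded as major violators, a definition that may sit in an analysis plan not shown. Finally, PP is one sensitivity analysis beside restricted mean survival.

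Much of this stands, and it rules out three stronger readings:

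- **That the rule deletes all of arm A's surgery failures.** R2 and explored-but-unresected patients have been operated on and can attend month 3.
- **That the bias in section 3 of the working is what will happen.** Those figures need every such failure dropped in arm A and kept in arm B. The documents do not establish that arm B keeps them.
- **That the trial's main conclusion is at risk.** The ITT test counts all these failures.

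The loose-wording defence does not clear the rule. With a Table 2 visit required in both arms, arm A patients on the full course must survive and be seen through about 12 more weeks than arm B patients, so selection still differs. Symmetric exclusion also still hides an excess of arm A failures. And the two anchors remain in conflict, so PP membership is not determined.

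**Conclusion.** The point holds in limited form. The PP visit rule is worded differently by arm, and the section on structured follow-up anchors those visits in two ways. On the Table 2 reading, the rule removes from arm A patients who never have surgery or who die before the first post-surgery visit, all of them DFS events, together with patients lost by then.

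The direction favours arm A. The size depends on failure rates the article does not give: with no true effect, an upper case of about 0.97 to 0.88 for rates of 1% to 5%. It is zero if both arms drop such patients at equal rates, apart from the longer pre-visit period in arm A, which was not quantified. An assumed excess of 5% against 2% disappears from view (1.08 to 1.00) even under symmetric exclusion. The damage is confined to the PP sensitivity analysis of DFS and its repeat for overall survival. The primary ITT result is untouched.

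**What to change.** Amend the PP definition so that one rule applies to both arms:

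- Drop the visit condition, or anchor the same condition at randomization in both arms.
- Keep every patient who already had a DFS event, including no surgery and early death, regardless of visits.
- Analyse the PP set by randomized arm, with crossovers excluded as major violations rather than moved to the other arm.
- Reconcile the two anchors in the text and in Table 2 of the structured follow-up section.

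The cost is one definition to amend and a slightly less selective PP set. No sample size, visit or data collection changes. Recruitment began in March 2025, so the change is best made now, before outcome data accumulate.

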### Safety analyses

Safety analysis will be performed in the safety set equivalent to the full-analysis set, specified above. Absolute and relative frequencies as well as unbiased event-rate estimates (Kaplan-Meier, Empirical cumulative incidence) of AEs, SAEs, event rates of grade 3 and 4 toxicities (NCI-CTCAE v5.0) and abnormal laboratory values/ increase/decrease between treatment arms will be reported at different time points together with 95%-confidence intervals. Safety of surgery is measured by complication scores (Clavien Dindo), R0/R1 resection rates, length of hospital stay, repeated operations due to complications, post-surgical infections, and anastomotic leaks. All analyses will be done using validated statistical software. The safety population for chemotherapy related toxicities comprises all patients who received at least one administration of FOLFOXIRI/FOLFOX-6 or CAPOX after randomization.

A Data and Safety Monitoring Board will oversee the study, conducting interim safety reviews and ensuring protocol adherence. Additionally, a Surgical steering committee has been established.

